**Fig. 6 Fig6:**
[figure not shown]
Legpress measurement

For the plantarflexion/dorsiflexion measurements, the participants lay in a supine position with their knee joints fully extended. The ankle joint’s axis of rotation is assumed to pass through the lateral malleolus and is visually aligned with the dynamometer’s axis of rotation. Axes alignment is performed at 90° ankle angle flexion (footplate relative to shank) which was determined using a handheld goniometer (Fig. 7). The test protocol comprises concentric plantarflexion and eccentric plantarflexion as well as eccentric dorsiflexion and concentric dorsiflexion with a velocity of 30°/s for both sides (4 repetitions each). The ROM is set to − 15° dorsiflexion to 20° plantarflexion.

**Fig. 7 Fig7:**
[figure not shown]
Isokinetic measurement

The same setup is used to measure the active and passive *ROM* of the participants. Therefore, the ankle is moved into maximal plantarflexion (+ °) and dorsiflexion (− °) either voluntary by the participant (active ROM) or by the investigator (passive ROM). During the passive movement, the participant is instructed to keep his muscles as relaxed as possible.

*Joint repositioning sense* of the plantarflexion/dorsiflexion movement is tested according to the study of Konradsen and Magnusson as well as Sefton et al. [48, 49]. It is determined by the participant’s ability to actively replicate a passively placed joint reference angle. The ankle will be passively moved into neutral ankle angle (90°), determined with a handheld goniometer, where it remains for a few seconds. It then will be passively moved through two full range of motion cycles. The participant is asked to actively reproduce the neutral reference angle. Three practice trials are followed by six test trials. Constant error will be calculated as the actual difference between the reference angle and the matching angle, with + or − indicating the direction of the error. The variable error will be calculated as the standard deviation of the constant error, indicating the error occurring when matching the reference angle. The absolute error will be calculated as the absolute value of the difference between the matching and reference angle, indicating the composite of both the systematic and random error [48].

*Kinematic data* is collected at 200 Hz using a portable motion capture system (myoMotion, Noraxon U.S.A. Inc., Scottsdale, Arizona, USA). Therefore, data of IMU are telemetrically transferred to the measurement software (MR3.16.58, Noraxon U.S.A. Inc., Scottsdale, Arizona, USA). The software is able to detect steps as well as jumps based on the input systems. The set of IMUs contain a total of seven sensors which are placed on pelvis, both femurs, tibiae, and feet. Straps are used to fix the sensors tightly in these locations (Fig. 8). The sensors are further attached with cohesive tape to reduce soft tissue artifacts and sensor displacement (Elastomull, BSN Medical, Hamburg, Germany). The pelvic sensor is applied over the first sacral spinous process. Upper leg sensors are placed at about 70% length of the femur over the tensor fasciae latae. Lower leg sensors are fixed over the bony surface at about 50% length of the tibia. Feet sensors are placed over the upper foot, slightly below the ankle. Sensor calibration takes place in a neutral upright position and re-calibration will be performed before each task to minimize sensor drift and electromagnetic interference which reduces data quality.

**Fig. 8 Fig8:**
[figure not shown]
EMG and IMU placement

*Electromyography* is performed using surface EMG. We use eight telemetric EMG sensors (TeleMyo DTS EMG, Noraxon U.S.A. Inc., Scottsdale, Arizona, USA) sampling data at 1500 Hz with a 10–500 Hz bandpass filter. EMG signals were further rectified and processed using a moving average root mean square (RMS) algorithm. Peroneus longus, tibialis anterior, gastrocnemius medialis, and rectus femoris are selected to analyze (Fig. 8). Two ECG surface electrodes (Ambu Blue Sensor N, Ambu GmbH, Bad Nauheim, Germany) per muscle are applied according to SENIAM guidelines. They are placed in parallel following the muscle fiber direction with an approximate inter-electrode difference of 2 cm. Skin preparation includes shaving of the defined area, followed by the removal of dead skin cells with an abrasive paste (Everi, Spes Medica, Battipaglia, Italy) and by cleaning with isopropyl alcohol. The EMG sensors are wired to the electrodes and attached to the skin with kinesiologic tape (PINO Pharmazeutische Präparate GmbH, Hamburg, Germany).

Raw data of IMU, EMG, treadmill, force plates, and the motorized dynamometer are synchronized in the measurement software.

### Plans to promote participant retention and complete follow-up [18b]

As already mentioned in 11b, there are multiple strategies to promote the participant’s adherence to the intervention. There will also be check-ups during the 6-week-intervention. These are video calls which are attractive to the participant since they provide a low-threshold access to the intervention. These check-ups help to guide the intervention and eventually adapt it. The 6-month follow-up will be done via email with Heartbeat (service to collect questionnaires). By this, the participants can answer the questionnaires from home. Heartbeat will send reminders to the participant in case of not answering the questionnaire. There will be a list of all expected outcomes for the patients. The participants will get an expense allowance after 6 weeks and 12 months. By dividing disbursement of the expense allowance to the 6-week and 12-month time points, patients are further encouraged to complete their follow-up. In case a participant does not want to complete the follow-up, especially the diagnostic, we give the option to just complete the questionnaires via Heartbeat.

### Data management [19]

Experimental data of the measurement software (gait/run analysis, jump analysis, static postural control, and strength measurement) will be exported individually into excel files right after data collection (Microsoft Excel 2016, Redmond, USA). SEBT data, ROM, strength measurements of the peroneus muscle, and measurements of the joint positioning sense testing will be documented by paper forms, created by the study team, which will later be transferred to electronic. Hard-copy data of the paper-forms will be stored for a period of 10 years after completion of the study in separate file folders. Proms (CAIT & FAAM) are collected via Heartbeat medical APP (service to collect questionnaires) which can also be transferred into excel files after checking the data. All data will be transferred into a prepared mother table. Everything is stored on two secure servers within the hospital computer system. Only the study team will be given access to the study folders where the database is saved. Further, a password system will be utilized to control access. All the data are checked before being transferred to the statistical software for analysis. Data integrity will be enforced by referential data and range checks by two separate sport scientists. Within the ethics approval, there is an individual data protection policy on disclosure/ data collection, data management, data labelling, and data protection.

### Confidentiality [27]

Data will be kept pseudonymized with an individual trial identification number in folders with limited access, only by members of the trial team to ensure confidentiality. All records that contain names or other personal identifiers will be stored separately from study records. All local databases will be secured with password-protected access systems.

### Plans for collection, laboratory evaluation, and storage of biological specimens for genetic or molecular analysis in this trial/future use [33]

Not applicable as there is no laboratory evaluation or biological specimen collection in this study.

## Statistical methods

### Statistical methods for primary and secondary outcomes [20a]

As introduced earlier, there is a primary aim and a secondary aim of the study. While the primary aim is investigated as a longitudinal study, the secondary aim of the study is to have a comparison from injured to non-injured participants. Therefore, statistical analysis of both approaches differs:

#### Primary study aim

The primary outcome, CAIT, will be analyzed with a repeated-measurement ANOVA using JASP (JASP 2018, Amsterdam, Netherlands). The same will be done for some secondary outcome measurements like FAAM, postural control, joint repositioning sense, jump, and strength metrics.

Continuous data (isokinetic measurements, IMU and EMG data of gait, run and jumps, ground reaction forces) will be analyzed via SPM. Most statistical test procedures are often based on the assumption of simple Gaussian distribution and reduce data complexity by comparing maxima, minima, or mean data. Instead of reducing data complexity and the underlying informational content of continuous variables, SPM allows for probalistic inferences regarding any kind of smooth, bounded continuous parameters [50, 51]. All SPM analyses are implemented using the open source spm1d code (v.M0.1, www.spm1d.org) in Matlab (R2014a, 8.3.0.532, The Mathworks Inc, Natick, MA).

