### Outcomes [12]

#### Primary outcome measurement

The primary outcome measurement is the subjectively perceived ankle joint function. This is measured by the standardized questionnaire Cumberland Ankle Instability Tool (CAIT). The difference in change in score between two groups will be assessed. The method of aggregation is mean ± SD, and the CAIT will be measured before and after the 6-week intervention as well as in the 6-month and a 12-month follow-up (Table 1).

**Table 1 Tab1:** Primary and secondary outcome measurements

Primary	Secondary
CAIT	FAAM
	mod. SEBT and COP
	Joint repositioning sense
	ROM
	Gait and run analysis
	Jump analysis
	Strength diagnostic

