### Participant timeline [13]

The process of enrolment (eligibility screen, informed consent, basic sociodemographic data) will take place in the first 2 weeks after initial injury. At t1, before the 6-week intervention, participants will be allocated and there will be psychometric questionnaires as well as all strength, postural control, gait/run, and jump testing. The same will be done at t2 after the intervention. While t3 is just a follow-up done by email, t4 includes the full diagnostic standard as in t1 and t2 (Fig. 1).

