### Sample size [14]

The sample size was calculated for the primary outcome (CAIT) and a repeated-measurement ANOVA with G*Power [42]. Therefore, the following assumptions were used: effect size *f* = 0.5, *α* = 0.05, statistical power (1 − *ß* = 0.80), two groups (SMART and NORMT), and four measurements (t1, t2. t3, t4). The effect size was set according to Wright et al. [43]. This resulted in a total sample size of 82 patients (2 × *n* = 41). With an accounted lost to follow-up of 20%, a sample size of 102 (2 × *n* = 51) is necessary to prove statistic group differences.

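### The repeated-measures ANOVA keeps only complete series, so a patient who stays in the trial but misses one assessment is dropped from that outcome's longitudinal comparison

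*Protocol article*

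**What the plan says.** Under Statistical methods [20a], Primary study aim: "The primary outcome, CAIT, will be analyzed with a repeated-measurement ANOVA using JASP". The same method is assigned to some secondary outcomes: FAAM, postural control, joint repositioning sense, jump and strength metrics.

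The schedule comes from three sections.

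- **Primary outcome measurement:** "CAIT will be measured before and after the 6-week intervention as well as in the 6-month and a 12-month follow-up". That makes four scores per patient. FAAM follows the same schedule. The laboratory outcomes are taken at t1, t2 and t4.
- **Participant timeline [13]:** "While t3 is just a follow-up done by email".
- **Retention [18b]:** for patients unwilling to complete the follow-up, especially the diagnostics, "we give the option to just complete the questionnaires via Heartbeat". Data collection [18a] identifies the Heartbeat questionnaires as CAIT and FAAM.

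Section [11b] allows a diagnostic test that a patient cannot perform to be adapted or skipped and recorded as not feasible. Section [20c] says, for the primary aim, only that patients who withdraw are left out of the analysis. For the secondary aim it keeps every randomised participant. Sample size [14] reaches 82 patients, then adds the allowance "With an accounted lost to follow-up of 20" percent and arrives at 102.

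**The concern.** A classical repeated-measures ANOVA needs a full row of data for each patient. With four CAIT times, one missing score removes the patient and the three scores that were collected. The patients at issue have not withdrawn, so the rule in [20c] does not reach them. Even if that rule were changed to keep everyone randomised, the ANOVA named in [20a] could not use an incomplete series.

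The t3 questionnaire is the likeliest gap. It is completed at home, and the two payments fall at 6 weeks and 12 months, so none is tied to it.

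For the laboratory outcomes the protocol itself creates incomplete series, through the questionnaire-only option and through skipped tests. A patient with t1 and t2 strength results but no t4 test would be missing from the longitudinal group comparison of strength, including its end-of-treatment part.

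Two things are at stake. Data already collected go unused. And the patients lost may differ from those kept: people who do not answer e-mail, who decline testing at 12 months, or who could not perform a jump early on. The protocol's background links inability to perform a drop landing and drop vertical jump within 2 weeks of injury to later CAI. The allocation is open and the payments differ by arm (2 × 50 € for SMART, 2 × 25 € for NORMT), so the loss could also differ by arm.

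**Working it through.** **1. Who is dropped, outcome by outcome**

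| Situation of a continuing patient | CAIT and FAAM ANOVA (t1–t4) | Laboratory ANOVA (t1, t2, t4) | Cross-sectional secondary aim (t1, t2) |
|---|---|---|---|
| Misses the t3 e-mail questionnaires | Dropped | Kept | Kept |
| Questionnaires only at t4 | Kept | Dropped | Kept |
| One test skipped at t1 as not feasible | Kept | Dropped for that test | t2 result kept |

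**2. The plan's own inflation step**

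Inputs from Sample size [14]: 82 analysable patients, 20% loss, 102 in total.

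- 82 / (1 − 0.20) = 102.5, against the stated 102. The step reproduces within rounding.
- 102 × 0.80 = 81.6. If the whole allowance is used, nothing is left over.

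**3. When the allowance is enough**

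The protocol gives no rate of missed assessments, so the rate p is my assumption. With no withdrawals and independent missingness p at each of t2, t3 and t4, complete cases = 102 × (1 − p)³.

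| p per visit | (1 − p)³ | Complete cases of 102 |
|---|---|---|
| 3% | 0.913 | 93 |
| 5% | 0.857 | 87 |
| 7% | 0.804 | 82 |
| 10% | 0.729 | 74 |

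About 7% per visit uses up the allowance with no withdrawals at all. Below that, it is sufficient.

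**4. When it is not enough**

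Suppose instead that the full 20% is lost and a further share q of those remaining miss one CAIT. Complete cases = 81.6 × (1 − q). The total needed to keep 82 is 82 / (0.8 × (1 − q)).

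| q | Complete cases | Total needed |
|---|---|---|
| 2% | 80 | 105 |
| 5% | 78 | 108 |
| 10% | 73 | 114 |
| 20% | 65 | 129 |

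**5. Can this be turned into a loss of power?**

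The plan states "effect size *f* = 0.5". It gives no correlation between visits, so I assume ρ = 0.5. The between-group test has noncentrality λ = N f² m / (1 + (m − 1)ρ), with m = 4 and degrees of freedom 1 and N − 2.

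- At f = 0.5 this needs N = 22, not 82. Power is still above 0.99 at N = 60.
- N = 82 appears at f = 0.25, with power 0.808. There, 78, 73 and 65 complete cases give 0.79, 0.76 and 0.71.
- Primary outcome measurement defines the comparison as a difference in change, which is group by time. With λ = N f² m / (1 − ρ), f = 0.25 and sphericity, power is above 0.99 at 82 and 0.998 at 60. Under the worst-case sphericity correction (ε = 1/3) it is 0.95 at 82 and 0.87 at 60.

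The answer depends on which effect size and which test are taken, so no single power loss can be assigned to this trial.

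**The case against.** The strongest reply has four parts.

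**Questionnaire-only t4.** A reader might infer that patients who take this option lose all their data. They do not. The option delivers CAIT and FAAM, so it protects the primary analysis. Only the longitudinal laboratory comparisons lose them, and their t1 and t2 results still enter the comparison with uninjured controls. This part stands in full.

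**The 20% allowance.** A reader might infer that missed questionnaires necessarily come on top of it and push the evaluable number below 82. The protocol does not say whether its loss figure includes missed assessments, and step 3 shows that moderate missingness fits inside it. This also stands.

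**Power.** Values of about 0.7 hold only for a between-group main effect at f = 0.25, which is neither the stated effect size nor the stated comparison of change. They cannot be presented as the trial's power loss.

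**Mitigation and level of detail.** Automatic reminders and a list of expected outcomes are planned, and a separate analysis plan could say how single gaps are handled. Reminders lower the rate but do not bring it to zero. On the second point, the protocol does not merely leave a detail open. It names a method that, as ordinarily run, cannot use an incomplete series. That part of the concern survives.

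**Conclusion.** The concern holds in a limited form. As written, the primary analysis drops a continuing patient for one missed CAIT, and the scalar laboratory ANOVAs drop a patient for one missing test. The withdrawal rule neither causes nor cures this.

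The loss is potentially selective and wastes collected data. Its size is unknown. The allowance has no slack (81.6 against 82), but it is insufficient only if withdrawals and missed assessments together exceed about 20%.

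The conclusion assumes the ANOVA is run in its standard complete-case form with no imputation; the protocol mentions none. The missingness rates and the correlation of 0.5 in the working are illustrations, not figures from the protocol. The case for change rests on selection and unused data, not on a demonstrated shortfall in power.

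**What to change.** In Statistical methods [20a], Primary study aim, replace the repeated-measures ANOVA for CAIT, FAAM and the scalar laboratory outcomes with a linear mixed model for repeated measures: group, categorical visit and group by visit, with an unstructured covariance across visits. Each patient then contributes every visit observed. Add a sentence that a missed t3 questionnaire, or a t4 without laboratory testing, does not remove the patient's other visits. In Sample size [14], say whether the 20% covers missed assessments as well as withdrawals.

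The cost is a different procedure on the same data and revised wording, with no new patients or visits. The model assumes that missing values are missing at random given the observed data. That assumption should be stated, since non-response may depend on how the ankle is doing.

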#### Secondary study aim

The primary study outcome, CAIT, will be analyzed with an unpaired *t*-test, comparing injured patients with the uninjured control group. The same will be done for some secondary outcome measurements like FAAM, postural control, joint repositioning sense, jump, and strength metrics.

Continuous data (isokinetic measurements, IMU and EMG data of gait, run and jumps, ground reaction forces) will be analyzed via SPM, as described above.

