### Objectives [7]

The *primary aim* of the study is to investigate the effectiveness of a sensorimotor training intervention (SMART-Treatment, SMART) in contrast to standard therapy (Normal Treatment, NORMT) after an acute first-time LAS on perceived ankle joint function. We hypothesize that patients treated with SMART show a better subjective outcome in perceived ankle joint function than patients treated with NORMT.

The *secondary aim* is to determine an effective test battery for the valid measurement of a functional ankle instability. This will be achieved by comparing injured patients (2 weeks after initial injury, t1, as well as after the training intervention, t2) with an uninjured control group (CONTROL).

While primary aim of the study is studied in a longitudinal manner, the design of the secondary aim of the study can rather be classified as a cross-sectional study. Therefore, both study arms work independent from each other, and each have an own statistical approach.

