### Eligibility criteria [10]

#### Inclusion criteria

Patents must meet the following criteria to be eligible for the study:ICD-Code S93.4x “sprain of the ankle”14–41 yearsBMI 19–30MRI confirmed lesion or rupture of at least one lateral ankle ligament

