#### Exclusion criteria

If the patients meet any of the following criteria, they will not be eligible for the study:Acute concomitant injuries of the ankle (fractures, syndesmosis ligament injury, osteochondral lesions)Pre-injuries of the injured and non-injured ankleSerious lower-extremity injuries of the last 6 months (e.g., fractures, ligament ruptures)Lower-extremity surgery (e.g., ACL-reconstruction)Neurological diseases or impairments of the vestibular system which could influence the physiological performance

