**Fig. 5 Fig5:**
[figure not shown]
Single-leg drop landing

The *strength* diagnostic will be performed in a motorized dynamometer (IsoMed, D. & R. Ferstl GmbH, Hernau, Germany) which is able to measure bilateral force (N) production in a closed kinetic chain as well as plantarflexion and dorsiflexion torque (Nm) in an open kinetic chain. There will be isometric as well as isokinetic (concentric/eccentric) lower limb strength measurements and measurements of the plantar- and dorsiflexors (concentric/eccentric and eccentric/concentric). For all tests, the participants will be fixated with two shoulder restraints, one waist strap, and an additional restraint over the distal thigh during the plantarflexion/dorsiflexion to secure them firmly to the dynamometer and prevent compensatory movement.

The legpress measurements include maximal isometric voluntary contractions (3 repetitions with 1 min rest) at 90° hip flexion, 90° knee flexion, and neutral foot position which is determined using a handheld goniometer as well as a dynamic (concentric extension/eccentric extension) test protocol (6 repetitions) with a range of motion (ROM) from 90° knee flexion to approximately 10° knee flexion (determined using handheld goniometer). The movement speed is set to 120 mm/s (Fig. 6).

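### The comparison of patients with the non-randomised CONTROL group rests on an unadjusted t-test, so a sex, age or body-size imbalance can mimic or hide a strength or jump deficit

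*Protocol article*

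**What the plan says.** Objectives [7] sets the secondary aim: to determine a test battery by comparing injured patients, two weeks after injury (t1) "as well as after the training intervention, t2) with an uninjured control group (CONTROL"). The article adds that "the design of the secondary aim of the study can rather be classified as a cross-sectional study". Sequence generation [16a] allocates participants to SMART and NORMT only, so CONTROL is outside the randomisation.

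Statistical methods [20a], Secondary study aim, fixes the method. The CAIT "will be analyzed with an unpaired *t*-test, comparing injured patients with the uninjured control group". It continues: "The same will be done for some secondary outcome measurements like FAAM, postural control, joint repositioning sense, jump, and strength metrics". Isokinetic, kinematic, EMG and ground reaction force data go to SPM. No covariate is named for either method.

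On scale, the strength device is described as able to "measure bilateral force (N) production in a closed kinetic chain as well as plantarflexion and dorsiflexion torque (Nm"), and Outcomes [12] gives strength in those units. Jump height, contact time and the index derived from them are reported unscaled. The mod. SEBT is the exception: reach is normalised to leg length.

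The Eligibility criteria [10] are worded for patients. The inclusion list states what they "must meet the following criteria to be eligible for the study", including a sprain code and an MRI-confirmed ligament lesion. The exclusion list opens "If the patients meet any of the following criteria, they will not be eligible for the study".

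**The concern.** A t-test between two groups that were not formed by randomisation estimates the injury effect plus whatever else differs between the groups. Absolute force, torque and jump height vary with sex, age and body mass. If the volunteers in CONTROL differ from the patients in these respects, that difference enters the group contrast in full, and an unpaired t-test cannot remove it.

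The Discussion says the purpose is to find tests that reveal abnormal ankle function and to use them in guiding later rehabilitation. A strength or jump test could be picked because of who volunteered. A useful test could be dropped because the imbalance ran the other way.

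**Working it through.** The article gives no sample size, sex split or expected difference for the CONTROL comparison, so there is no plan figure to reproduce. What follows shows how sensitive the named test is.

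**Inputs**

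- Patients: 82, the article's total before allowance for loss (Sample size [14]), used here as the number compared.
- Controls: 41, assumed. 82 is tried as an alternative.
- True ankle deficit: zero.
- Sex difference D on absolute strength: 1.0, 1.5 or 2.0 within-sex SD, assumed.
- Share of males: 60% in one group and 40% in the other (gap g = 0.20), assumed.
- Test: unpaired t, two-sided 5% (sidedness assumed), df = 82 + 41 − 2 = 121, critical value 1.980.

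**Step 1: shift in within-sex SD.** Shift = g × D, which gives 0.20, 0.30 and 0.40.

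**Step 2: convert to the SD the t-test uses.** Each group mixes the sexes, so its SD is √(1 + p(1 − p)D²). With p = 0.6 or 0.4, p(1 − p) = 0.24 in both groups.

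- D = 1.0: √1.24 = 1.114; shift 0.20/1.114 = 0.18
- D = 1.5: √1.54 = 1.241; shift 0.30/1.241 = 0.24
- D = 2.0: √1.96 = 1.400; shift 0.40/1.400 = 0.29

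**Step 3: rejection rate.** Noncentrality = shift / √(1/82 + 1/41) = shift / 0.191. The rate comes from the noncentral t.

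| D | Shift (pooled SD) | Noncentrality | Rejects, 82 v 41 | Rejects, 82 v 82 |
|---|---|---|---|---|
| 1.0 | 0.18 | 0.94 | 15% | 21% |
| 1.5 | 0.24 | 1.26 | 24% | 34% |
| 2.0 | 0.29 | 1.49 | 32% | 44% |

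More controls make the false signal more likely to reach significance, because the bias does not shrink with sample size.

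**Step 4: wider gap.** At 65% v 35% male, p(1 − p) = 0.2275. The shifts are 0.27, 0.37 and 0.43, and the rejection rates at 82 v 41 are 29%, 48% and 61%.

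**Step 5: masking.** For a true deficit of 0.5 SD, power at 82 v 41 is 74%. An imbalance of 0.2 SD in the opposite direction leaves an apparent 0.3 SD, and power falls to 34%.

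**Is the imbalance handled elsewhere?**

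- Leg-length normalisation covers body size for the mod. SEBT only.
- The additional analyses split participants by age group and perhaps activity level. That is a subgroup look, not an adjustment of the CONTROL contrast.
- No matching or frequency balancing is stated.

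**The case against.** - **Entry rules may exist elsewhere.** This is a condensed article; the full protocol, the supplement and the schedule figure are not shown. Recruitment rules for a healthy comparison group may well sit there. This stands. A reader might infer that controls may be of any age, sex or BMI, or may have old sprains, or that they fall outside every entry criterion. The article says none of this. A control can meet the age and BMI limits and pass the exclusions, and sex is not restricted for patients either. All that can be said is that the text shown applies no entry criterion to CONTROL.
- **The t-test does not cover everything.** It is named for the CAIT and some other measures, while isokinetic and ground reaction force data go to SPM. This stands, and it widens the remedy: the SPM comparisons with CONTROL need the same covariates.
- **Several outcomes are less exposed.** The mod. SEBT is normalised and also yields between-leg differences. The body-size argument does not carry over to the CAIT, the FAAM or repositioning error. This stands; the calculation concerns absolute strength.
- **The error rates are assumed.** Group size, sex gap and imbalance are all supplied here. This stands. A reader might take 15% to 61% as properties of this plan, but no actual imbalance has been shown.
- **An unseen analysis plan might add covariates.** Possible, but the article names the test, and an unpaired t-test has none. Entry limits would not settle this either: two groups aged 14–41 with BMI 19–30 can still differ in sex mix.

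**Conclusion.** The point holds for the stated analysis. A non-randomised comparison is tested without adjustment on measures that include absolute strength and jump height, and nothing in the article balances sex, age or body mass. Under the assumed 20-point sex gap, the spurious shift is 0.18 to 0.29 pooled SD and the false-positive rate is 15% to 32% with 41 controls, against a nominal 5%. These figures illustrate sensitivity; the real bias could be near zero or larger, in either direction. The absence of entry criteria for CONTROL is something to check against the full protocol, not an established defect. Only the secondary aim is touched: the randomised SMART v NORMT comparison does not use CONTROL. The change should be made, but the trial's main result does not depend on it.

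**What to change.** 1. In Statistical methods [20a], Secondary study aim, replace the unpaired t-test with a linear model containing group, age, sex and body mass, fitted at t1 and at t2. Report the adjusted group difference with its confidence interval.
2. Use the same covariates in the SPM comparisons with CONTROL. Changing the t-test alone would leave the isokinetic, kinematic, EMG and force comparisons unadjusted.
3. As a supporting check, report the injured-versus-uninjured limb contrast within patients for measures taken on each side, such as plantarflexion and dorsiflexion torque, single-leg stance and single-leg drop landing. Sex, age and body mass cancel in this contrast, and the exclusions already rule out earlier injury of the other ankle. It cannot be formed for the bilateral drop jump outcomes, and it assumes the other limb is unaffected.
4. If the full protocol does not already do so, apply the age and BMI limits and the listed exclusions, reworded for people without an injury, to controls.

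**Cost.** Three covariates use three degrees of freedom, and the analysis takes slightly more work. Age, sex and body mass must be recorded for controls as well as patients. If entry limits are added, some volunteers may be turned away. With recruitment under way since January 2022, items 1 to 3 can still be adopted without changing who has been enrolled, provided those data are available.
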